### 10.3 Other study parameters

Cost-effectiveness analyses are performed according to the intention-to-treat principle. For the economic evaluation, missing data are imputed using multiple imputation by chained equations. To deal with the highly skewed nature of cost data, 95% CIs around the differences in costs are estimated using the Bias Corrected and Accelerated Bootstrap method, with 5000 replications. Incremental Cost-Effectiveness Ratios (ICERs) are calculated by dividing the difference in costs by that in QALYs (cost-utility) or by that in 'disease-specific' physical functioning (cost-effectiveness). This will be measured by the EQ5D5L questionnaire and an economic costs questionnaire which quantify absenteeism from paid work as well as productivity losses related to unpaid labor. To graphically illustrate the uncertainty surrounding the ICERs, bootstrapped incremental cost-effect

pairs are plotted on cost-effectiveness planes. A summary measure of the joint uncertainty of costs and effects is presented using Cost-Effectiveness Acceptability Curves (CEACs), which indicate the probability of an intervention being cost-effective in comparison with the control condition for a range of willingness-to-pay values (i.e. the maximum amount of money decision-makers are willing to pay to gain one extra unit of effect).

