## 8. METHODS

### 8.1 Study parameters/endpoints

#### 8.1.1 Main study parameter/endpoint

Number of infants with an ipsilateral recurrent hernia or MCIH after operative repair requiring a reoperation within one year after primary surgery.

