#### Definitions

*Testicular atrophy*: Complete testicular atrophy: no palpable testicular tissue in scrotum.

*Partial testicular atrophy*: Testis documented to be smaller at follow-up than at time of inguinal hernia repair.

*Wound infection/Surgical site infections*: Infection, occurring within 30 days of surgery, involving only the skin and subcutaneous tissue. Purulent discharge or organisms isolated from aseptically obtained wound culture must be present. Also at least one of the following signs of infection must be present: Pain or tenderness, localized swelling and redness or heat.

*Apnoea*: An unexplained episode of cessation of breathing for 20 seconds or longer, or a shorter respiratory pause associated with bradycardia, cyanosis, pallor, and/or marked hypotonia.

Total duration of surgery (including anaesthesia) related to primary open or laparoscopic inguinal hernia repair.

Postoperative pain measured according to the children and infants post-operative pain score (CHIPPS) and VAS and pain medication requirement related to post-operative pain within 2 weeks after primary operation.

Length of hospital stay related to inguinal hernia within one year after primary operation.

Time to full recovery within one year after primary operation.

CPPV rate during laparoscopic contra-lateral exploration in the PIRS group. When seen, the CPPV will be corrected.

MCIH rate within one year after primary operation.

Cosmetic appearance scored on a 5-Likert scale from 1-5 (1= bad, 2=unsatisfactory, 3=satisfactory, 4=good, 5=excellent) within one year after primary operation. Cosmetic appearance will be scored 4 weeks and 1 year after primary surgery.

Cost-effectiveness will be assessed from a societal and health care perspective and will include cost of surgery, hospitalization, control visits, re-operation, complications and loss of productivity of the parents/caretakers. Most data will be registered in the medical records; specific data entry forms will be used. Data on productivity loss will be collected by online questionnaires before surgery, four weeks after surgery, one year after surgery and in case of a recurrence or MCIH, four weeks after re-operation. Cost of the operation will be measured using a bottom-up micro costing approach. Other costs will be valued using guideline prices.

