#### Assessment of study parameters/endpoints

The following applies to all infants admitted to the hospital for inguinal hernia repair included in this study.

Preoperative size of both testes, the number of operations per infant, length of hospital stay, total duration of operations (including anaesthesia) and perioperative complications of surgery (iatrogenic injury, apnoea) will be recorded in Case Report Forms by the (fellow) paediatric surgeon. One telephone call is performed by a member of the research team after four weeks in the control and intervention group to obtain information regarding recovery of the patient, wound healing and recurrence. Pre-operative and four weeks and one year post-operative, parents or patients older than 12 years of age (with the aid of their parents) will fill out an online questionnaire regarding health of the subject and cost-effectiveness. Invitations for the questionnaires will be sent by Castor EDC, in which the results also will be recorded (13). Furthermore one and two years after surgery telephone call is conducted to assess post-operative complications such as testicular atrophy and recurrence. Prior to the telephone consult, parents are asked to send a photo to the researcher with the help of a secured online application (SURFfilesender) and a coded number

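### Section 10.3 plans a cost-effectiveness ratio per unit of disease-specific physical functioning, but the questionnaires it names do not yield that score and the visible protocol defines it nowhere else

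*Protocol*

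**What the plan says.** Section 10.3 divides the cost difference in two ways: by the difference in QALYs, and by the difference in disease-specific physical functioning. On the second ratio and its source it reads: "physical functioning (cost-effectiveness). This will be measured by the EQ5D5L questionnaire and an economic costs questionnaire". By the description given there, the costs questionnaire covers absence from paid work and lost unpaid productivity. The section then plans cost-effectiveness planes and acceptability curves, the latter over a range of willingness to pay for one further unit of effect.

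Section 8.1.2 describes the economic endpoint by its cost items alone: it "will include cost of surgery, hospitalization, control visits, re-operation, complications and loss of productivity of the parents/caretakers". It names no effect measure. Section 8.3 says that parents, or patients over 12 with their parents' help, "will fill out an online questionnaire regarding health of the subject and cost-effectiveness", before surgery, at four weeks and at one year. It does not name the questionnaire or list its contents.

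The primary endpoint in section 8.1.1 is: "Number of infants with an ipsilateral recurrent hernia or MCIH after operative repair requiring a reoperation within one year after primary surgery".

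**The concern.** A ratio needs a measured denominator. For the cost-effectiveness ratio, section 10.3 names a quantity and then names instruments that do not produce it. This goes beyond missing detail that an analysis plan could add. An analysis plan can define how collected data are scored, but it cannot supply data from a scale that was never given to the families. What is administered, and when, is a protocol matter.

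Cost-effectiveness is part of the trial's stated objective in the Summary and in section 1. If the denominator stays undefined, the second ratio may be dropped without comment, or an effect measure may be chosen after the results are known. The acceptability curve for that ratio also has no unit on its willingness-to-pay axis.

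**Working it through.** Section 10.3 gives no figure to reproduce on this point, so the check sets the passages side by side.

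1. **What the second ratio needs.** It is (difference in mean cost) / (difference in mean disease-specific physical functioning). The denominator needs a scale, a scoring rule and at least one time point in both arms.

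2. **What the named instruments give.**
   - EQ5D5L: a generic health-status profile. It serves the QALY ratio. The protocol mentions no disease-specific module or item.
   - Economic costs questionnaire: by the protocol's own description, absenteeism from paid work and lost unpaid work. It feeds the numerator and does not describe the child's functioning.

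3. **Whether another section supplies the measure.**
   - Summary and section 2: the endpoint lists contain no physical functioning.
   - Section 8.1.1: reoperation only.
   - Section 8.1.2: complications, duration of surgery, pain, hospital stay, time to full recovery, CPPV rate, MCIH rate, cosmetic appearance and cost-effectiveness. No functioning score is listed.
   - Section 8.1.3: not applicable.
   - Section 8.3: an unnamed online questionnaire on health and cost-effectiveness.
   - Section 12.1: the data list has no functioning item.

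   The term occurs once in the visible document, in section 10.3, in inverted commas and without a scale, score or time point.

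4. **What is affected.** Of the two stated ratios, one (QALY) has a named instrument and one (functioning) does not. The plane and the acceptability curve for the second fall with it. The cost difference with its bootstrap interval, the imputation and the whole cost-utility analysis do not use the functioning score.

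5. **Whether a denominator is already in the data.** Yes. The primary endpoint is recorded for each child at one year, and costs are collected for the same children. The replacement ratio is

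   (mean cost PIRS − mean cost open) / (proportion reoperated, open − proportion reoperated, PIRS).

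   Under the planning rates in section 4.4 the denominator is 0.06 − 0.01 = 0.05. Both parts can be computed in each bootstrap replicate, so the planned planes and curves carry over unchanged. Reoperation cost stays in the numerator, which makes the numerator a net cost.

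**The case against.** The strongest reply is that the visible protocol does not rule the scale out. The contents of the section 8.3 questionnaire are not listed, section 8.1.2 mentions specific data entry forms, and Appendix 1 is blacked out. The word that opens the measurement sentence in 10.3 could refer to QALYs, functioning or costs, and the inverted commas suggest a loose term. This stands as far as it goes. A reader might infer that the ratio cannot be produced at all, and the documents do not support that. They support only that it has no stated data source, because 10.3 names two questionnaires and neither fits.

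Three further readings are tempting and do not hold.

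- A reader might infer that half of the economic evaluation has no data. The cost comparison and the cost-utility ratio are untouched; one ratio is under-defined.
- A reader might infer that the protocol fails to answer its main economic question, the cost of avoiding a second operation. The protocol never calls that its main economic question, and nothing in it requires the economic effect to be the primary endpoint. Leaving reoperation out of the denominators is a weakness of choice, not a contradiction. A rough point estimate could also be put together from the planned cost difference and the planned risk difference in section 10.1; what is not specified is the joint uncertainty.
- A reader might take 1/0.05 = 20, the factor from cost per child to cost per reoperation avoided, as the size of the defect. It only converts units under the planned difference and does not measure what the undefined term loses.

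**Conclusion.** The point holds in this form: the cost-effectiveness ratio in section 10.3 has a denominator that the named instruments do not yield and that no other visible section defines. Its size is one of two stated ratios, with its plane and curve. The primary endpoint, the sample size, the safety reporting, the cost comparison and the cost-per-QALY ratio are not touched.

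The conclusion rests on two assumptions. First, that the EQ5D5L is used in its ordinary generic form, since the protocol describes no adaptation. Second, that the section 8.3 questionnaire holds no unnamed disease-specific scale. If it does hold one, the defect reduces to a failure to name it. The point merits a correction, because a stated measurement does not match the stated quantity and the repair needs no new data.

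**What to change.** - In section 10.3, make the cost-effectiveness denominator reoperation for ipsilateral recurrence or MCIH avoided within one year, as defined in section 8.1.1, with the same bootstrap, planes and acceptability curves. Name the same effect measure beside the cost items in section 8.1.2.
- If a disease-specific functioning scale is already part of the section 8.3 questionnaire, name it with its time points in sections 8.1.2 and 8.3, and keep that ratio as well. Measured data should not be discarded.
- State in section 10.3 that the QALY difference is adjusted for the pre-operative score. Section 8.3 already plans a pre-operative health questionnaire. This assumes that the EQ5D5L is part of it, which the text should say.

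The cost is wording in sections 8.1.2, 8.3 and 10.3, with no new data collection. The one downside is that the effect unit of a secondary ratio changes.

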#### **10.4 Interim analysis (if applicable)**

An interim analysis will be performed after one year of follow-up to assess the effectivity of the laparoscopic versus open inguinal hernia repair. In case of a significant difference between the open or laparoscopic group, an analysis will be performed to see in the study can continue with a subgroup. If the study can continue with a subgroup, a new sample size calculation will be performed based on the characteristics this subgroup. If no significant difference is found during the interim analysis, the study will continue as stated in this protocol.

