### **4.4 Sample size calculation**

Reoperation includes both MCIH and recurrence rates. Since recent studies showed that the recurrence rate is similar between the open and laparoscopic group (0.3 vs 0.2% (12)), we used reoperation rates due to MCIH to calculate our sample size. The latest IPEG guidelines states that the MCIH rate after open repair is 6-8%. We expect that the laparoscopic repair reduces the MCIH rate to 1% since the CPPV will be closed during the same procedure. Thus, re-operation based on MCIH is performed in approximately 6% patients in the open group and in approximately 1% in the laparoscopic PIRS group. We consider a reduction of 5% of children requiring reoperation clinically relevant.

A total sample size of 422 patients is needed to detect such a reduction with a power of 0.80 at a two-sided alpha of 0.05 (nQuery Advisor 7.0). Taking into account 10% loss to follow-up we need to include 464 children. Since approximately 800-850 paediatric patients a year undergo inguinal hernia repair in our participating centres, we expect to reach our sample size within one to two years after the start of the trial. After one year of follow-up, we will perform an interim analysis to assess the effect of both treatment strategies.

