#### **8.7 Premature termination of the study**

The study will be terminated premature if new evidence has arisen that conclude that the effect of the treatment arm is inferior and it is therefore not ethical to continue treatment of more patients with this inferior arm.

In case the study is ended prematurely, the sponsor will notify the accredited METC within 15 days, including the reasons for the premature termination.

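### The interim efficacy look has no boundary or fixed information point, and a significant result may lead to continuing in an unnamed, data-chosen subgroup, so the two-sided 5% error is not protected

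*Protocol*

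**What the plan says.** Section 4.4 takes reoperation rates of 6% (open) and 1% (PIRS). Its total of 422 evaluable children rests on one test: "detect such a reduction with a power of 0.80 at a two-sided alpha of 0.05". It adds 10% for loss to follow-up, giving 464, and announces an interim analysis of the effect of both strategies after one year of follow-up.

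Section 10.4 describes that look as an assessment of effectiveness, with two branches:

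- **Significant:** "In case of a significant difference between the open or laparoscopic group, an analysis will be performed to see in the study can continue". The continuation meant is in a subgroup. If that is judged possible, the sample size is recalculated for the subgroup.
- **Not significant:** "If no significant difference is found during the interim analysis, the study will continue as stated in this protocol". The one-year chi-square test of section 10.1 then follows.

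The protocol does not say what level counts as significant at the look, how many children must have one-year data, which subgroups are eligible, how one is chosen, or how data from before and after the change are combined.

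**The concern.** Two things are at stake.

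**Repeated testing.** The same hypothesis is tested at the look and, if that test is not significant, again at the end. The sample size is that of a single test using the full 0.05. With no reduced level at either test, the chance of at least one false positive is above 5%.

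**The subgroup step.** A subgroup may be chosen from the data that triggered the choice, and the trial re-sized for it. With few events the choice is mostly noise, and reusing the same children in the later subgroup test biases that test. The final conclusion could then concern a population that nobody planned to study.

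**Working it through.** **1. The plan's own figure.** Inputs from section 4.4: 6% against 1%, two-sided 0.05, power 0.80. From section 8.2: 1:1 allocation. The average rate is (6% + 1%)/2 = 3.5%. With pooled variance and no continuity correction:

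n per arm = [1.960·√(2·0.035·0.965) + 0.842·√(0.06·0.94 + 0.01·0.99)]² / 0.05² = (0.5094 + 0.2167)² / 0.0025 = 210.9, so 211 per arm and 422 in total.

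This reproduces 422 exactly. It is the sample size for one test at the full 0.05.

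**2. Two looks, both at 0.05.** With information fraction t at the look, the two z-statistics are bivariate normal with correlation √t under no effect. The overall error is 1 − P(|Z₁|<1.96, |Z₂|<1.96). The protocol gives no t, so a range is shown. The simulation draws binomial outcomes at a 3.5% event rate in both arms with 422 children (100,000 runs per setting).

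| t (assumed) | Normal theory | Binomial simulation |
|---|---|---|
| 0.25 | 9.1% | 8.1% |
| 0.50 | 8.3% | 7.9% |
| 0.75 | 7.3% | 7.2% |

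At t = 0.10 and 0.90, normal theory gives 9.5% and 6.5%. Every fraction tested is above 5%.

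**3. Does a significant interim count as a finding?** Step 2 assumes that it does. Suppose instead that only the last test made counts, in the whole trial or in the subgroup. At t = 0.50 the simulation gave 7.93% for any rejection, 4.36% for a significant look, and 1.13% for a significant look followed by a significant subgroup test. The error is then 7.93 − 4.36 + 1.13 = 4.70%. The same sum gives 8.10 − 3.70 + 0.53 = 4.93% at t = 0.25 and 7.17 − 4.59 + 2.27 = 4.85% at t = 0.75.

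**4. The subgroup step.** Half of 422 is 211 children, and 211 × 0.035 = 7.4, so about 7 events are expected. As an illustration, take the four effect modifiers of section 10.1 as 50/50 splits. After a false-positive look, choose the best of the eight levels, enrol all remaining children from it, and test it at 0.05 with its interim data included. That test is significant in 14%, 26% and 49% of cases at t = 0.25, 0.50 and 0.75, against a nominal 5%.

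**5. Standard limits at t = 0.50.**

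| Limits (interim, final) | Overall error | Evaluable sample size for power 0.80 |
|---|---|---|
| p<0.001, 0.05 (Haybittle-Peto) | 5.02% | 422 |
| p<0.0031, 0.049 (O'Brien-Fleming-type spending) | 5.00% | about 424 |
| p<0.0052, 0.048 (classical O'Brien-Fleming) | 5.0% | about 425 |
| p<0.0294 at both (Pocock) | 5.0% | about 469 |

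**The case against.** The strongest reply is that section 10.4 says significant without naming 0.05, that nominal interim levels are often left to a SAP, and that one may exist here. A total of 422 does not rule out a conservative boundary, because step 5 shows that such a boundary hardly moves the sample size. This stands as a limit on the 8% figure. It does not cover the subgroup continuation and re-sizing, which are design changes written into the protocol.

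The timing is also open. If one year of follow-up means one year for every child, the primary endpoint is tested once and the repeated-look inflation disappears. The talk of an interim, of the study continuing and of a new sample size points to an earlier look. Even on the late reading, the subgroup extension would reuse the data that selected it.

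A reader might infer more than the documents support:

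- **That the false-positive rate certainly exceeds 5%.** Step 3 shows that this depends on whether a significant look counts as a claim, which the protocol does not settle.
- **That the trial will switch to a subgroup.** The text says only that an analysis will examine whether it can.
- **That a spurious subgroup has a 25% chance of appearing.** That is the chance that some level of the four factors reaches p<0.05 in all 422 children. At 211 it is about 18%, and about 3% to 4% once a significant overall look is also required. Under no effect those cases already lie within the first-look rejections. Section 10.4 also does not link its subgroup to those four factors.
- **That section 8.7 contradicts section 10.4.** Section 8.7 says "The study will be terminated premature if new evidence has arisen" that an arm is inferior. Section 10.4 states no stopping rule. Different triggers are not a contradiction.
- **That the look comes too late to be useful.** With uniform accrual over T months, 464·(T − 12)/T children have one-year data when enrolment ends: 0, 155 and 232 for 12, 18 and 24 months. These counts rest on uniform accrual and on a look at that moment, and the protocol fixes neither.

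**Conclusion.** The concern holds in this form. The protocol fixes an efficacy look triggered by bare significance, with no boundary or information point, beside a sample size for one test at two-sided 0.05. Followed as written, this does not protect the 5% error. The overall error is about 8% if both tests are at 0.05 and a significant look is acted on as a finding. The exact value depends on an information fraction that the protocol does not give.

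The open-ended subgroup continuation is the firmer part of the point, because it depends neither on the interim level nor on the timing. The 14% to 49% in step 4 shows the direction and rough scale of the bias under assumed factors and a simple selection rule. It is conditional on a false-positive look and does not add to the 8%.

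**What to change.** 1. In section 10.4, delete the two sentences on continuing with a subgroup and recalculating its sample size. Keep the effect-modification analyses of section 10.1 as exploratory. Named subgroups with a closed or combination test would also control error, but need considerably more design work.
2. Then choose one of two options and align the sentence in section 4.4:
   - drop the interim efficacy test; or
   - hold one look at a fixed point, for example when half of the children have one-year outcomes, with either a Haybittle-Peto limit (p<0.001, final about 0.05) or O'Brien-Fleming limits (about 0.005 interim, 0.048 final). State that a look that does not cross its limit leads to the unchanged final test.
3. If the look is kept, say who sees the result. Section 9.5 describes the safety committee only as helping when an SAE occurs, so this task would extend its remit.

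The cost is a short protocol amendment. The evaluable sample size stays at 422 with Haybittle-Peto and rises to about 424 or 425 with O'Brien-Fleming limits. The price is a stricter early threshold and the loss of the ad hoc subgroup option.

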## **8.2 Randomisation, blinding and treatment allocation**

When parents/caretakers provide informed consent, the child will be randomly assigned (1:1) to the intervention (laparoscopic repair) or control group (open repair) using a web-based application with a computer-generated list with random block sizes of four or six and rendered by an independent data manager. The block size of the randomisation scheme is unknown to the study personnel. Participants and investigators are aware of allocation; masking is impossible because of the nature of the intervention.

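### Section 10.4 acts on a significant interim difference without stating a level, while the final test keeps the full alpha of 0.05 and any continued subgroup is chosen after the result

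*Protocol*

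**What the plan says.** Protocol section 4.4 sizes the trial for one comparison of "approximately 6% patients in the open group and in approximately 1% in the laparoscopic PIRS group". It states: "A total sample size of 422 patients is needed to detect such a reduction". The calculation was made "with a power of 0.80 at a two-sided alpha of 0.05". The same section announces an interim analysis of the treatment effect.

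Section 10.4 makes that interim a comparison of effectiveness with two branches.

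- **Significant:** "In case of a significant difference between the open or laparoscopic group, an analysis will be performed to see in the study can continue". Continuation would be in part of the population only, and in that event "a new sample size calculation will be performed based on the characteristics this subgroup".
- **Not significant:** the trial carries on under the existing protocol. That leads to the chi-square test and 95% confidence intervals of section 10.1.

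Section 10.4 gives no significance level, no boundary, and no number of children or events at which the look takes place. It does not name the subgroup. Section 10.1 lists four effect modifiers: gestational age, age at surgery, sex and hernia side.

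**The concern.** The final test already uses all of the 5%. An earlier test of the same hypothesis that can trigger action, with no level of its own, gives the trial a second chance of a false positive that the sample size section does not count.

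The significant branch has a further problem. Results that cross a threshold midway overstate the effect on average. A subgroup picked after such a result, from several possible factors, is a selected one. The trial would also move away from its stated question, which concerns all children with a primary unilateral hernia. Allocation is open (section 8.2) and there is no DSMB (section 9.5), so a threshold fixed in advance is the main protection.

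This is more than a detail left to a later analysis plan. The protocol itself fixes the trigger, its consequence, the full-alpha sample size and the unadjusted return to the final test.

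**Working it through.** **Inputs.** From section 4.4: rates 6% and 1%, power 0.80, two-sided alpha 0.05, 422 evaluable children. From section 8.2: 1:1 allocation, so 211 per arm. From section 10.1: chi-square test. Assumed, because the protocol gives neither: an interim level of 0.05, and a look at 25%, 50% or 75% of the data.

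**1. Reproduce 422.** With the pooled-variance formula, n per arm = [1.96·√(2·0.035·0.965) + 0.8416·√(0.06·0.94 + 0.01·0.99)]² / 0.05² = (0.5094 + 0.2167)² / 0.0025 = 210.9. This rounds up to 211 per arm, 422 in total. The stated figure is the single-look size with nothing set aside for an interim.

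**2. Two looks at 0.05, normal approximation.** Overall error = 1 − P(|Z₁|<1.96 and |Z₂|<1.96), where the correlation of Z₁ and Z₂ is √t and t is the information fraction. The result is 0.091 at t=0.25, 0.083 at 0.50 and 0.073 at 0.75.

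**3. Two looks at 0.05, exact.** Events are sparse, so the chi-square test was also enumerated exactly over both stages (53, 105 or 158 per arm at the look, 211 at the end):

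| Common rate | 25% | 50% | 75% |
|---|---|---|---|
| 1% | 0.044 | 0.051 | 0.054 |
| 2% | 0.057 | 0.074 | 0.067 |
| 3.5% | 0.079 | 0.079 | 0.071 |
| 6% | 0.085 | 0.080 | 0.070 |

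A single final test has error 0.050 at 3.5%, 0.047 at 6% and 0.042 at 1%. The planning rates average (6% + 1%)/2 = 3.5%, so that row is the natural reference.

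**4. How often the significant branch opens.** At 6% v 1%, a look at 0.05 is significant in about 24% of trials at a quarter of the data and in about 52% at half (106 per arm). In those 52%, the mean observed difference is 6.8 points against a true 5.0, with on average 7.7 v 0.5 events. A subgroup choice made from the interim results would rest on roughly eight events.

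**5. Possible remedies.**

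- **p<0.001 at the look, 0.05 at the end.** Overall alpha is 0.050 at a 3.5% rate and 0.045 to 0.050 across 2% to 6%. Exact chi-square power at 211 per arm is 0.849 with or without the look (the sizing formula gives 0.800). The chance of crossing at half the data falls from 52% to 2.3%.
- **O'Brien-Fleming-type spending, look at half the information.** The nominal levels are 0.0031 and 0.0490. The sizing formula at 0.0490 gives 426 instead of 422, or 4 more children. The levels depend on timing: 0.000015 and 0.0500 at 25%, 0.0193 and 0.0442 at 75%.

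**The case against.** The strongest reply is that section 10.4 never says 0.05. The sizing alpha in 4.4 is not an interim threshold, and a very strict look would make the inflation negligible without contradicting any sentence of the protocol. Boundaries are also often placed in an analysis plan. The first part stands: a reader might infer that the protocol allots 5% to each look and that its alpha is therefore wrong as a matter of fact, but the text does not say so. The inflation is conditional. What remains is that the protocol makes significance the trigger for a major change, offers 0.05 as its only level, and returns to an unadjusted final test.

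Second, the timing is open. The endpoint counts events "requiring a reoperation within one year after primary surgery". If the interim waited until every child had one year of follow-up, it would be the primary analysis and there would be no second look. That reading cannot be excluded, but a possible continuation with a new sample size argues against it.

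Third, a reader might infer that the subgroup would be re-sized from the few interim events. Section 10.4 refers only to the subgroup's characteristics, and only if continuation is possible. Use of interim rates is not stated, so no error in the recalculated size is claimed here.

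Fourth, at a 1% null rate the overall error stays close to 0.05, because the chi-square test is conservative with so few events. This is correct, but 1% lies well below the 3.5% average of the planning rates.

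**Conclusion.** The point holds in conditional form. The protocol sets a significance-triggered effectiveness look with no level and leaves the full 0.05 at the final test. If the look is made at 0.05, the overall type I error is about 0.07 to 0.08 at a common rate of 3.5%, 0.057 to 0.085 across 2% to 6%, and 0.044 to 0.054 at 1%, for looks at 25% to 75% of the data. These figures rest on the assumed interim level and information fraction.

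The choice of an unnamed subgroup after a significant look adds further error. The protocol does not control it, and its size cannot be computed from the document. The documents do not support saying that alpha is definitely breached or that re-sizing would use interim rates. The level should be fixed before any interim comparison is made.

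**What to change.** In section 10.4, make one of these changes:

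- State that the interim difference counts as significant only at a strict pre-set level. Two-sided p<0.001 with the final test at 0.05 is one choice. An O'Brien-Fleming-type boundary is another (about 0.0031 and 0.0490 if the look is at half the information).
- Delete the interim effectiveness test.

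If continuation in a subgroup is kept, limit the candidates to the four effect modifiers in section 10.1. State that the result in all children is the answer to the trial's question. Label any continued-subgroup result exploratory unless its error is controlled, for example by a combination test.

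**Cost.** The p<0.001 rule is a change of wording, with no more children and no loss of power. The O'Brien-Fleming-type boundary adds about 4 children. The price of p<0.001 is a lower chance of an early declaration: at half the data under 6% v 1%, about 52% falls to about 2%. A confirmatory subgroup claim is not free. If it were tested only on new children and sized at the planning rates, it would need about 422 more evaluable children.
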